### Trial design {8}

This is a mechanistic, sham-controlled, randomized, parallel design, multi-site (2 sites), clinical trial in which participants with chronic SCI are assigned in equal ratios to one of three study groups (or arms). Group 1: Active transspinal stimulation while standing followed by locomotor training; Group 2: Active transspinal stimulation while lying supine followed by locomotor training; and Group 3: Sham transspinal stimulation while standing followed by locomotor training. Study outcomes are assessed for superiority before (baseline) and after 40 sessions of primed locomotor training.

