### Sample size {14}

Our study is powered to establish and detect a significant effect size across the 3 groups between pre- and post-intervention. We performed statistical analysis of the preliminary data utilizing G*Power-3 software [88, 89]. The sample size was calculated to obtain a power larger than 0.8.

*Aim 1:* Determine if priming locomotor training with transspinal stimulation increases MEP amplitudes and promotes appropriate MEP amplitude modulation during stepping. The TA MEPmax amplitudes recorded in 10 healthy subjects while at rest were compared before and after 10 sessions of transspinal stimulation delivered with subjects lying supine (difference between means: 148.05, pooled standard deviation: 206.8, d = 0.71). To predict sample size at a power of 0.80 at α = 0.05 using repeated measures, within-between interaction ANOVA across 3 groups, 24 total subjects are needed. We will enroll 45 subjects, so we will be adequately powered even if subjects drop out at a higher than expected 20% rate. This sample size is based on results from healthy control subjects and not from SCI subjects.

*Aim 2*: Determine if priming locomotor training with transspinal stimulation restores spinal inhibition, reduces neurophysiological hyperreflexia, and re-establishes H-reflex modulation during stepping. The soleus H-reflex rate-dependent depression in 6 persons with SCI was recorded at 1.0 Hz from the left leg and compared before and after 15 sessions of transspinal stimulation. Based on the soleus H-reflex recorded at 1.0 Hz before and after transspinal stimulation (difference in means of pre versus post: 25.28, pooled standard deviation: 28.92), the effect size was 0.87. To predict sample size at a power of 0.80 at α = 0.05 using a one-way ANOVA across 3 groups, 18 total subjects are needed. We will enroll 45 subjects, so we will be adequately powered even if subjects drop out at a higher than expected 20% rate.

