The soleus H-reflex amplitude during assisted stepping in 11 persons with motor incomplete SCI (AIS C-D) recorded from the right leg was compared before and after locomotor training [26]. Based on the amplitude of the soleus H-reflex at mid-stance before and after training (difference in means of pre versus post: 13.67, pooled standard deviation: 17.4), the effect size was 0.79. To predict sample size at a power of 0.80 at α = 0.05 using a one-way ANOVA across 3 groups, 21 total subjects are needed. We will enroll 45 subjects, so we will be adequately powered even if subjects drop out at a higher than expected 20% rate.

Limb coordination relies on the strength of reciprocal inhibition between antagonistic muscles. We used data from a study performed by our group that examined short-latency inhibition from ankle flexor afferents onto ankle extensor motoneurons at rest in 13 persons with AIS C-D SCI before and after locomotor training [28]. Based on the amplitude of the conditioned H-reflex at the conditioning-test interval of 2 ms before and after training (difference in mean of pre versus post: 15.04, pooled standard deviation: 17.21), the effect size was 0.874. To predict sample size at a power of 0.80 at α = 0.05 using a one-way ANOVA across 3 groups, 18 total subjects are needed. We will enroll 45 subjects, so we will be adequately powered even if subjects drop out at a higher than expected 20% rate. Please note that the established power was based on data from SCI subjects who received either transspinal stimulation or locomotor training separately and not combined.

*Aim 3*: Determine if priming locomotor training with high-frequency transspinal stimulation improves limb coordination and the ability to stand and walk. These are secondary measures, and the study is not powered based on these outcomes.

Collectively, an average of 6 to 8 subjects per group is needed to establish significant differences for primary outcomes before and after transspinal stimulation or locomotor training. By enrolling 15 participants per group, the study will be robustly over-powered to detect these differences despite a projected possible 20% dropout rate, sporadic missing data values, or lower-than-expected observed effect sizes.

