## Assignment of interventions: allocation

### Sequence generation {16a}

To minimize imbalance between study groups, we performed block randomization with a block size of 9 to assign eligible participants into the 3 groups. If groups are not balanced, we ensure that the following blocked randomized subjects are stratified based on their ability to ambulate with assistive devices or not. We will also check after the completion of intervention by all subjects in each group, whether the groups are balanced or not regarding baseline motor function and perform tests of association accordingly. Blocked randomization is a commonly used randomization technique in clinical trials with a small sample size. This approach reduces bias and fosters balanced allocation of participants into different groups [90].

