### Implementation {16c}

The randomization scheme is accessible only to the biostatistician who generated it (PA). Assignment allocations are released by the biostatistician to other study personnel once each new participant has completed consent and all screening procedures. The sequence of assignments to groups is random and therefore appropriately concealed.

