### Procedure for unblinding if needed {17b}

Staff members who perform the thoracolumbar electrical stimulation and the biostatistician who performs the allocation are not blinded. We do not anticipate any requirement for unblinding but if required, the investigators will have access to group allocations and any unblinding will be reported. Data will be unblinded when data analysis is completed and statistical tests between study groups need to be performed.

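### The randomisation scheme may change mid-trial on an undefined look at arm balance, and a single disclosed block of 9 with unblinded stimulation staff leaves part of the sequence deducible

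*Protocol article*

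**What the plan says.** Under Sequence generation {16a}, the protocol article states that "we performed block randomization with a block size of 9 to assign eligible participants into the 3 groups". It then adds a contingency: "If groups are not balanced, we ensure that the following blocked randomized subjects are stratified based on their ability to ambulate with assistive devices". After all participants have finished, the investigators will also check "whether the groups are balanced or not regarding baseline motor function and perform tests of association accordingly".

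Under Implementation {16c}, only the biostatistician can see the list, and each allocation is released after that participant has consented and completed screening. The section concludes: "The sequence of assignments to groups is random and therefore appropriately concealed".

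Under Procedure for unblinding {17b}: "Staff members who perform the thoracolumbar electrical stimulation and the biostatistician who performs the allocation are not blinded". Trial status gives recruitment as running from March 2021 to about April 2025, so the block size was disclosed while allocation was still under way.

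Statistical methods {20a} plans, for every outcome and without any condition, a repeated measures ANCOVA whose covariates include clinically evaluated baseline walking function. Site is not among them.

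**The concern.** There are two separate problems.

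First, stratification is not a feature set at the start. It is switched on for later participants if the arms accrued so far look unbalanced. The text leaves open whether balance refers to numbers, ambulation or motor function, and gives no threshold, timing or decision-maker. This is a rule that is stated but badly fixed, not a detail left to another document. Nobody could reconstruct from it how a given participant's allocation was generated. Opening two strata part-way can also leave blocks incomplete, which works against the equal arm sizes that blocking otherwise guarantees.

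Second, a single known block size lets anyone who has followed earlier allocations work out some of the later ones, most easily at the end of a block. Stimulation staff know what they deliver. A random sequence can still be deducible, so the inference from randomness to concealment in {16c} does not hold. At stake is whether knowledge of a coming allocation could influence who is enrolled and when.

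**Working it through.** **Inputs.** Three arms, "assigned in equal ratios to one of three study groups (or arms") (Trial design {8}). Block size 9, so 3 per arm per block ({16a}). Total 45: "We will enroll 45 subjects" (Sample size {14}).

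**The plan's own figure.** 45/9 = 5 complete blocks, and 5 × 3 = 15 per arm. This reproduces the 15 per group in Sample size {14}. Without a switch the split is always 15/15/15.

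**Effect of the switch.** The article does not say how blocks would work within strata. The assumptions here are two strata, blocks of 9 in each, and one stratum holding 50% or 30% of participants. There were 20,000 simulated trials per setting.

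| Switch after | Mean largest-minus-smallest arm (50% / 30%) | Exact 15/15/15 (50% / 30%) |
|---|---|---|
| 9 | 1.54 / 1.56 | 33.0% / 32.6% |
| 18 | 1.77 / 1.49 | 25.4% / 34.6% |
| 27 | 1.36 / 1.88 | 39.0% / 22.3% |
| 36 | 2.03 / 1.80 | 17.9% / 23.8% |

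The largest difference seen was 6 in every setting. Without the switch it is 0.

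**Predictability of a known block of 9.** The observer is assumed to know the block size and every earlier allocation in the block.

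- *Certain assignments.* The last one is always certain. The last two are certain if they fall in the same arm, with probability 2/8. The last three are certain with probability (2/8)(1/7). The expected number is 1 + 2/8 + (2/8)(1/7) = 1.286 per block. That is 1.286/9 = 14.3%, or 5 × 1.286 = 6.4 of 45.
- *At least one arm ruled out* (including the certain ones). Exact enumeration gives 3.214 per block, which is 35.7%, or about 16 of 45.
- *Best guess* (the arm with most places left). Exact enumeration gives 4.787 correct per block, which is 53.2%, or 23.9 of 45. Chance gives 33.3%, or 15 of 45.

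**Which block sizes would help.** With fixed, known blocks the best guess succeeds 61.1% of the time for size 3, 56.1% for 6, 53.2% for 9 and 51.2% for 12. Smaller blocks are therefore worse. For mixed, undisclosed sizes, the check was a simulation of lists of 45 with sizes equally likely, guessing whichever arm has been used least so far. This strategy needs no knowledge of the sizes. It succeeds about 57% of the time for a 3/6 mix and about 52% for a 6/9/12 mix, against about 53% for a fixed 9. The 6/9/12 mix barely changes the guess rate. Its gain is that an observer who does not know where blocks end can no longer be certain of the last places.

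**The case against.** **Safeguards.** The article does describe a concealment procedure: the list is held centrally and allocations are released only after consent and screening. This stands, and it prevents anyone from seeing the next allocation. It does not prevent deduction from past ones.

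**Upper case.** The 14% and 53% require one observer to know all earlier allocations in order. There are two sites, and the article does not say whether there is one list or one per site. Staff who see only their own site's allocations would do less well. Section {17a} states that the locomotor training, clinical assessment and analysis personnel are blinded, and nothing says that stimulation staff screen or enrol. This stands. A reader might infer that enrolment has been steered, but the documents do not support that.

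**Error rate.** A reader might infer that a data-dependent switch leaves the type I error of the planned tests undefined. The text does not support this either. The stated trigger is group balance, the stratifier is a baseline characteristic, and no outcome data are mentioned. Allocation stays blocked and random after the switch.

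**Numerical imbalance.** Stratifying aims at balance on ambulation, and a mean arm difference of 1.4 to 2.0 is small. This is fair, and the size depends on an assumed block structure. It remains a cost for something the planned covariate largely supplies already.

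**End-of-trial check.** One might read the tests of association as letting a baseline comparison choose the analysis model. The wording is too vague to establish that, and the ANCOVA in {20a} is planned unconditionally.

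**Conclusion.** The point holds in a limited form. The conditional restratification is undefined, so the allocation procedure is neither fixed in advance nor reproducible. This rests on the text alone. The loss of exact balance (15/15/15 in about 18% to 39% of runs instead of always) rests on assumed blocks of 9 in two strata with shares of 30% to 50%.

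The disclosed single block size makes up to 14% of assignments certain and up to 53% guessable, for an observer with full knowledge of earlier allocations. The sentence deriving concealment from randomness is wrong as reasoning, although the procedure described before it has real value. Neither selection bias nor type I error inflation is demonstrated. The change is worth making because it is cheap, and because new block sizes can only help participants not yet randomised.

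**What to change.** 1. Delete the conditional restratification in {16a} and keep one scheme to the end. If the switch has already been used, report when and on what criterion.
2. Rely on the baseline walking function covariate already planned in {20a}, state that it applies whatever the end-of-trial balance check shows, and add site.
3. For participants not yet randomised, have the biostatistician draw the remaining list in varied block sizes that include larger ones, for example 6, 9 and 12. Keep the sizes out of any document open to site staff. A mix of 3 and 6 should be avoided, because it raises best-guess success to about 57%.
4. Rewrite the closing sentence of {16c} so that concealment rests on central list-holding, release after screening and undisclosed block sizes, not on randomness.

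The cost is a short amendment and one new list. Arm sizes may end slightly unequal if the last block is incomplete. Balance on ambulation by design is slightly looser, and the covariate adjustment recovers this.

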### Concealment mechanism {16b}

The randomization scheme was generated by a trained biostatistician using R software [91].

### Implementation {16c}

The randomization scheme is accessible only to the biostatistician who generated it (PA). Assignment allocations are released by the biostatistician to other study personnel once each new participant has completed consent and all screening procedures. The sequence of assignments to groups is random and therefore appropriately concealed.

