#### Locomotor training

After 30 min of transspinal stimulation all participants receive 30 min of locomotor training with the Lokomat 6 Pro (Hocoma, Switzerland). Over the training course, we use a clinical algorithm to adjust BWS, ankle straps position, and leg guidance force [26]. The tension of the ankle straps is adjusted based on the right and left TA muscle strength evaluated every week. BWS and leg guidance force are adjusted based on presence or absence of knee buckling during standing. BWS, ankle straps position, and leg guidance force are individualized as is the case during outpatient rehabilitation. All intervention and training sessions are supervised by at least two of the authors.

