### Outcomes {12}

#### Primary outcomes

The primary outcomes are neurophysiological biomarkers that accurately probe corticospinal and spinal neuroplasticity (at presynaptic and postsynaptic motoneuron levels):Corticospinal neuronal excitability:

We establish the active MEP threshold that corresponds to the intensity that evokes 10 responses of at least 50 mV following 20 1-ms transcranial magnetic stimulation (TMS) pulses in seated subjects. Then, the soleus MEP recruitment input–output curve is assembled while maintaining small-amplitude contractions. During BWS-assisted stepping, MEPs are recorded at 1.3 times the right soleus MEP active threshold randomly at different phases of the step cycle (divided into 16 equal bins or time windows) based on the signal from the right foot switch. During stepping, MEPs are collected before and after intervention using Lokomat settings matched to the baseline, while an effort is made to record MEPs using Lokomat settings matched to those of the last training session. This establishes changes at matched settings and adaptations during more demanding stepping conditions. MEPs recorded at different stimulation intensities (recruitment curve) are measured as peak-to-peak amplitude and normalized to the soleus maximal M-wave (Mmax) evoked by posterior tibial nerve stimulation to counteract differences in muscle fiber composition across subjects. Stimulation intensities are normalized to the intensity corresponding to the 50% of the MEPmax amplitude, estimated based on the sigmoid function fit to the data. For the participants who have obtainable soleus MEPs at baseline, the main outcomes from this experiment are the MEPmax from the MEP recruitment curves and the MEP amplitude at the mid-stance and mid-swing phases before and after the intervention.2)Spinal neuronal excitability:*2a) Soleus H-reflex rate-dependent (or homosynaptic) depression*: To assess restoration of homosynaptic depression exerted at the synapses between muscle spindle primary Ia afferents and alpha motoneurons, soleus H-reflexes following posterior tibial nerve stimulation at the popliteal fossa with a 1-ms pulse are recorded from seated subjects at different frequencies (1.0, 0.33, 0.2, 0.125, and 0.1 Hz). Homosynaptic depression is greatest at 1.0 Hz and fully recovers at 0.125 and 0.1 Hz [69]. Homosynaptic depression cannot be recorded during stepping because it is abolished by strong spinal inhibitory circuits and efferent activity. The main outcome measure from this neurophysiological biomarker is the soleus H-reflex 1.0/0.1 Hz ratio [70].*2b) Soleus H-reflex depression by antagonistic nerve stimulation*: To examine the restoration of reciprocal inhibitory actions on antagonistic alpha motoneurons, the soleus H-reflex is conditioned by common peroneal nerve (CPN) stimulation at conditioning-test (C-T) intervals of 0, 1, 2, 3 and 4 ms, with subjects seated [71–75]. Reproducible CPN conditioning stimulation is ensured by using a stable, small-amplitude TA M-wave and similar soleus M-wave amplitudes under control and conditioning stimulations. Soleus H-reflexes are measured as peak-to-peak amplitude, accepted for M-waves ranging from 2 to 8% of the maximal M-wave (Mmax), and normalized to the Mmax. The main outcome is the amplitude of the conditioned soleus H-reflex as a percentage of the control H-reflex. The C-T interval for which reciprocal inhibition is present or reciprocal facilitation is the smallest is further investigated during BWS-assisted stepping. The main outcomes are the conditioned H-reflex at rest and during the stance and swing phases of BWS-assisted stepping, which both reflect the amount of reciprocal inhibition.*2c) Control and conditioned soleus H-reflexes during stepping*: During standing with BWS as needed, the soleus H-reflex and M-wave recruitment curves are assembled. Then, each participant steps with the assistance of the Lokomat, and soleus H-reflexes are recorded under control conditions and following CPN conditioning stimulation randomly across 16 equal time bins into which each step cycle is divided based on the signal from the foot switch [75]. The tibial nerve stimulation intensity is adjusted in real-time online to evoke H-reflexes such that their corresponding M-waves are 2–8% of the Mmax evoked 80 ms after the test H-reflex at each bin (Fig. 3). Control and conditioned soleus H-reflexes during stepping are collected before (baseline) and 1–2 days after completion of all 40 intervention sessions at Lokomat settings matched to baseline and the last training session. This approach determines changes at matched settings and reflex adaptation at more demanding settings [76]. During stepping, soleus H-reflexes are measured as peak-to-peak amplitude, accepted for M-waves ranging from 2 to 8% of the Mmax, normalized to the Mmax, and averaged for each bin of the step cycle. The main outcome is the control and conditioned soleus H-reflex amplitude normalized to the Mmax at mid-stance and mid-swing phases.

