### Participant timeline {13}

The schedule of events for each participant enrolled in this study is presented in Fig. 4. *Enrollment − t*_*1*_*:* Obtain informed consent. Review medical history and medications to determine eligibility based on inclusion/exclusion criteria. Perform medical and neurological examinations needed to determine eligibility based on inclusion/exclusion criteria. Schedule study visits for participants who are eligible and available for the duration of the study. Provide participants with specific instructions needed to prepare for their first study visit, including but not limited to clothing prior to the study. *Baseline visit t*_*1*_*:* Record vital signs. Perform a Lokomat familiarization session. Perform clinical evaluation tests. *Baseline visit t*_*2*_*:* Record vital signs. Record MEPs at rest and during stepping with Lokomat settings obtained from the familiarization session. Provide to the participant the TMS side-effect questionnaire. Record adverse events as reported by participants or observed by investigators. *Baseline visit t*_*3*_*:* Record vital signs. Perform electrophysiological recordings (soleus H-reflex rate-dependent depression and reciprocal inhibition, control, and conditioned soleus H-reflex during BWS-assisted stepping). Record adverse events as reported by participants or observed by investigators. *Intervention visits 4–43:* Administer the assigned transspinal stimulation-locomotor training intervention. Reassess transspinal stimulation threshold and locomotor EMG activity at study Intervention visits *t*_*15*_ and *t*_*30*_. *Final study visits t*_*44*_* and t*_*45*_: Perform clinical evaluation tests and electrophysiological recordings as described in Baseline visits.

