## Assignment of interventions: blinding

### Who will be blinded {17a}

Participants will be blinded to group allocation. Participants allocated to the sham group will receive stimulation at motor threshold intensity for 1 min, followed by a gradual return to no stimulation to mimic the initial sensation of stimulation followed by the acclimation to cutaneous stimulation. The study personnel performing locomotor training, clinical assessments, and data analysis will be blinded to the group allocation. Because each participant’s study code is not linked to the group assignment, those who perform data analysis cannot recognize the study group of a participant.

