## Oversight and monitoring

### Composition of the coordinating center and trial steering committee {5d}

The principal investigators (PIs) of this clinical trial are PI # 1, [name], PT, MBA, PhD, at the College of Staten Island, City University of New York, and PI # 2, [name], PhD, at Icahn School of Medicine at Mount Sinai and James J. Peters Veterans Affairs Medical Research Center (JJPVAMC). PI # 1 performs along with her research team at the Klab4Recovery all neurophysiological recordings before and after training for all study participants of the clinical trial to ensure consistent experimental procedures for all neurophysiological recordings. PI # 1 also leads the implementation of transspinal stimulation and locomotor training interventions, as well as the clinical assessments before and after training for study participants at Klab4Recovery. PI # 2 leads the implementation of transspinal stimulation and locomotor training interventions as well as the clinical assessments before and after training for study participants at JJPVAMC. Both PIs ensure that locomotor training and transspinal stimulation are implemented equivalently at both sites. The trial steering committee is composed of the PIs and dedicated research staff.

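### Masking of the staff who record the primary neurophysiological outcomes is neither stated nor assured, and the release rule permits allocation to be known before the baseline recordings

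*Protocol article*

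**What the plan says.** **Primary outcomes.** Under Outcomes {12}: "The primary outcomes are neurophysiological biomarkers that accurately probe corticospinal and spinal neuroplasticity". The MEP main outcomes apply only to participants in whom a soleus MEP can be obtained at baseline.

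**Who records.** Under Composition of the coordinating center {5d}: "PI # 1 performs along with her research team at the Klab4Recovery all neurophysiological recordings before and after training for all study participants". Section {18a} adds that the same investigator takes the baseline and final measurements.

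**Who leads stimulation.** The same section {5d} says "PI # 1 also leads the implementation of transspinal stimulation and locomotor training interventions" for participants at Klab4Recovery. For the Veterans Affairs (VA) site it says "PI # 2 leads the implementation of transspinal stimulation and locomotor training interventions as well as the clinical assessments before and after training". The Locomotor training section says: "All intervention and training sessions are supervised by at least two of the authors".

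**Who is blinded.** Section {17a} covers participants and then states: "The study personnel performing locomotor training, clinical assessments, and data analysis will be blinded to the group allocation". Section {17b} names the staff who perform stimulation and the allocating biostatistician as not blinded. It places unblinding of the data after data analysis, when the group tests are due.

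**When allocation is released.** Implementation {16c}: "Assignment allocations are released by the biostatistician to other study personnel once each new participant has completed consent and all screening procedures". The Participant timeline {13} puts consent and the eligibility examinations at enrolment. At t2 it says "Record MEPs at rest and during stepping with Lokomat settings obtained from the familiarization session", and the H-reflex recordings follow at t3.

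**The concern.** The secondary clinical measures have stated assessor masking. The primary measures do not. Recording them is not a passive readout: the operator tunes tibial nerve intensity live during stepping, evokes MEPs while the participant holds a weak contraction, and places electrodes. If the operator knows the arm, those judgements can move with it.

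Two things are at stake. One is the measured values, both at baseline and after 40 sessions. The other is the composition of the MEP analysis set. If obtainability is judged after allocation is known, entry to a primary analysis becomes a post-randomisation decision by someone who may know the arm, and the comparison loses part of the protection that randomisation gives it.

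**Working it through.** No figure in the plan needs reproducing. The check sets the statements on roles and timing side by side.

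**1. Is recording covered by another blinded role?** Section {17a} blinds three staff roles. The nearest is clinical assessment, but Study setting {9}, {18a} and {5d} all treat neurophysiological recording and clinical assessment as separate activities, and {9} and {5d} assign them to partly different places and people. Recording is therefore not covered by that term. Section {17b} does not list recorders as unblinded either. They appear on neither list.

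**2. Does recording overlap with an unblinded role?** At Klab4Recovery, one investigator leads both recording and stimulation. At the VA site another investigator leads stimulation, while the Klab4Recovery team still records those participants. The stated overlap thus concerns participants treated at Klab4Recovery. The article does not say how many of the 45 that is. Standing versus supine delivery is visible to anyone present at a session; active versus sham while standing is not distinguishable by posture.

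**3. Can allocation be known before the primary baselines?**
- Condition for release: consent and all screening complete ({16c}).
- Time of screening: enrolment, before t1 ({13}).
- Time of the primary baselines: t2 for MEPs, t3 for H-reflexes ({13}).

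The condition can be met before t1, and nothing in the text delays release until t3. Confidentiality {27} fits this order: the study code is given at randomisation and used to save all data, which would include the baseline files. This is consistent with early randomisation but does not prove it.

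**4. How would a recording bias enter the analysis?** With two time points, the group-by-time interaction in section {20a} compares mean change between arms. Let b(pre) and b(post) be the differences between two arms in operator-induced shift at baseline and at the end. Then

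expected difference in observed change = true difference + b(post) − b(pre).

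A shift at either visit enters at full weight. It cancels only if b(pre) = b(post). Having the same investigator at both visits improves consistency but does not secure that equality. Releasing allocation after t3 removes knowledge of the arm as a source of b(pre). Masking recorders at t44 and t45 is needed to limit b(post). Neither part of the remedy does the work of the other.

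**The case against.** A reader might infer that the primary outcomes are unmasked. The documents do not support that. The article is silent about recorders, and {17b} confines the unblinded roles to those who perform stimulation and the biostatistician. Leading the implementation of stimulation is not the same as delivering it, and the individuals who record are not identified. A journal article may leave delegation of roles to a fuller document. The remark that authors supervise every session does not settle the matter, because it does not say which authors record.

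A reader might also infer that allocation is always released before baseline. The text sets a condition, not a date. It does not say that recorders are among the recipients, and the schedule figure is not shown.

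The recording rules also leave less freedom than a bare list of operator choices suggests. Sweeps are accepted only within an M-wave window of 2–8% of Mmax, amplitudes are normalised to Mmax, stimuli fall at random across 16 bins, MEP threshold has a response-count definition, and the conditioning-test interval follows a selection rule. Data analysis is done on codes not linked to group.

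All of this stands and limits the point. What remains is that the article does give explicit lists of blinded and unblinded roles, omits the primary-outcome recorders from both, assigns recording and stimulation leadership to one person at one site, and states a release rule that does not protect the baseline. Blinded analysis cannot undo choices made during acquisition or change who was judged to have an obtainable MEP.

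**Conclusion.** The concern holds in a limited form: masking of the recorders of the primary outcomes is neither stated nor assured, and the release rule permits allocation to be known before the t2 and t3 recordings and before MEP obtainability is judged. The timing gap applies to every participant; the overlap in leadership is stated for Klab4Recovery only.

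The size of any bias cannot be derived from the document. It gives no data on operator effects, no split of participants by site and no expected number with an obtainable MEP, so no effect on error rates is claimed. The conclusion rests on two readings: that screening means the enrolment examinations in the timeline, and that neurophysiological recording is distinct from clinical assessment, as the article treats it throughout. If recorders are in fact masked and release in practice follows t3, the defect is in the wording alone. The change is worth making because it costs little and protects the primary comparison.

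**What to change.** 1. In Implementation {16c}, make release conditional on completed t2 and t3 baseline recordings and a recorded decision on MEP obtainability.
2. In Who will be blinded {17a}, add neurophysiological recording, before and after the intervention. Where feasible, assign it to existing team members who do not deliver that participant's stimulation. Participants treated at the VA site fit this most easily.
3. Code files for participant and visit before sweeps are accepted or rejected.
4. Reconcile {17a} with {5d}: training and clinical assessment staff are declared blinded, yet each principal investigator leads stimulation, training and clinical assessment at their own site. State who performs each task.

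For participants already randomised, report when allocation was released and who recorded. The cost is a timing change by the biostatistician, a role assignment within existing staff and a small scheduling constraint at the main site. Sample size, visits and treatment are unchanged. If masked recording is already the practice, stating it takes one sentence.
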